#### 6.7 Major secondary analyses

The secondary endpoints include proportion of patients with moderate-to-good EULAR response rate at month 6 and month 12, ACR/EULAR Boolean remission rate month 6 and month 12, the change in simplified disease activity index (SDAI) month 6 and month 12, the change in clinical disease activity index (CDAI) month 6 and month 12, the change in tender joint count and swollen joint count month 6 and month 12, the change in Hospital Anxiety and Depression Scale (HADS) month 6 and month 12, the change in the 36-Item Short Form Survey (SF-36) month 6 and month 12, and flare rate at month 6 and month 12, the rate of patients with DAS28-CRP (CRP)  $\leq 3.2$  at month 12. The number and rate of adverse events. The normal distribution of the numeric variables will be examined using the Kolmogorov-Smirnov test. SDAI is continuously, while CDAI, swollen joint count, HADS and SF-36 are discrete variables. They will be used as continuous variables in this study. Descriptive data will be compared between the two arms using the student's t test for normally distributed data and Wilcoxon rank-sum test for data that are not normally distributed.

For all categorical secondary endpoints, the differences between the two groups and associated 95% confidence intervals (CIs) will be calculated using the Cochran-Mantel-Haenszel with adjustment for center effects. For non-normal distributed continuous and discrete variables, the differences in medians and associated 95% CIs will be analyzed using quantile regression with adjustment for center effects. The median difference of outpatient visits between the two arms were calculated with the use of the Hodges-Lehmann estimated based on the Mann-Whitney U test.

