### 3.6 Statistical analysis

All endpoints will be analyzed in a modified intent-to-treat (ITT) population that excluded patients with incorrect diagnosis (autoimmune diseases other than RA) upon enrolment. Sensitivity analysis will be performed to assess the robustness of the primary analysis using multiple imputation, last observation carried forward imputation, and the worst case scenario imputation. The primary endpoint will also be analysed using the per-protocol (PP) analysis, inverse probability of censoring weighted (IPCW) method. Continuous variables are defined as mean (standard deviation, SD) or median (inter-quartile range, IQR) and will be compared between the two groups using the Student's t-test or Wilcoxon

rank-sum test. Categorical variables are defined as frequency or percentage and compared between the two groups using  $\chi^2$  or Wilcoxon rank sum test, as appropriate. The trend of changes in DAS28-CRP and EULAR responses was calculated from baseline to month 6. Preplanned subgroup analyses will be conducted based on disease activity at baseline. Other subgroup analyses were post hoc. Statistical significance are set at 2-sided  $P < .05$ . All data analyses are conducted using the using the SAS and R.

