## 6. Statistical Procedures

### 6.1 Introduction

Mobile health applications (apps) have been shown to be effective in the management of chronic diseases with simple treatment target (e.g., hypertension). The potential clinical value of mobile health apps in RA has not been well studied.

The objective of this study is to investigate whether assessing patient reported outcomes using mobile health apps could result in improving outcomes in RA patients. This is a multicenter, randomized controlled trial in 22 tertiary hospitals across China. Eligible participants are adult RA patients with a smartphone. RA patients, regardless of baseline disease activity, will be included in this study. All patients will be followed up for 12-month. The statisticians and rheumatologists who assessed DAS28-CRP are blinded. Investigators and participants are not blind to group assignment. Participants will be randomly assigned at a 1:1 ratio (block size of four) to a smart system of disease management (SSDM) group or a conventional care control group. Upon the completion of 6-month parallel comparison, patients in the conventional care control group will be instructed to use the SSDM app for an extension of 6 months. The primary outcome is the rate of patients with DAS28-CRP  $\leq 3.2$  at month 6.

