### 6.3 Sample Size Determination

1) The rate of DAS28-CRP  $\leq 3.2$  at month 6 is assumed 44.3% in the control group and 52% in the SSDM group; 2) 2-sided  $\alpha$  at 0.05 and power at 90%; 3) 20% attrition rate. The calculation yields a total of 2200 patients. And 2204 is the minimum sample size created by the Random Number Generator.

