#### 6.6 Primary endpoint analysis

The primary outcome is the rate of patients achieving DAS28-CRP (CRP)  $\leq 3.2$  at month 6. The categorical variables are described by frequency or percentage. We will report the differences between the two groups and associated 95% confidence intervals (CIs) using the Cochran-Mantel-Haenszel with adjustment for central effects. A nominal significance level of 0.05 (two-sided) will be applied to all the analyses. The statistical analyses and reporting will follow the CONSORT guidelines.

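### Continuous secondary scores: a normality pretest chooses the method, and neither the baseline value nor the randomisation stratum is adjusted for

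*Combined protocol and SAP*

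**What the plan says.** SAP 6.7 covers change in SDAI, CDAI, tender joint count (TJC), swollen joint count (SJC), HADS and SF-36 at months 6 and 12. The first step is a pretest: "The normal distribution of the numeric variables will be examined using the Kolmogorov-Smirnov test". Variables judged normal go to a t test and the others to a Wilcoxon rank-sum test. For non-normal continuous and discrete variables the effect estimate is also named: "the differences in medians and associated 95% CIs will be analyzed using quantile regression with adjustment for center effects". No effect estimate, interval or centre adjustment is named for variables that pass the pretest. The section calls CDAI, SJC, HADS and SF-36 discrete but says they will be handled as continuous.

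Protocol 3.6 is no more specific: continuous variables "will be compared between the two groups using the Student's t-test or Wilcoxon" rank-sum test.

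Baseline information appears in three other places:
- Protocol 3.3 (2) stratifies randomisation on baseline DAS28-CRP in three levels, and the follow-up plan in 3.3 (4) collects SDAI, CDAI, HADS, SF-36 and DAS28-CRP (hence the joint counts) at month 0.
- SAP 6.4 adjusts for the baseline strata, but only in a logistic regression for binary variables.
- SAP 6.9 uses baseline characteristics as auxiliary variables for imputation, not as covariates in the analysis.

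**The concern.** Three features of SAP 6.7 deserve attention.

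First, the test, the effect measure (mean or median) and whether centre is adjusted for all depend on a test applied to the trial's own data. The analysis of each score is therefore not fixed in advance. SAP 6.9 adds a complication: endpoints are analysed in five imputed data sets and pooled, and nothing says what happens if the pretest disagrees between them.

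Second, subtracting baseline is a less efficient use of it than including it as a covariate, and the stratification factor is left out for these endpoints although the SAP includes it for binary ones. The cost is wider intervals than the data allow, for six sets of scores.

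Third, joint counts are whole numbers. A difference in median change can sit at 0, or step by one joint, when the distributions have shifted by a fraction of a joint. The report could then pair an effect estimate of 0 with a significant rank test.

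**Working it through.** **The plan's own figure.** The only sample size is for the primary binary endpoint. SAP 6.3: the rate "is assumed 44.3% in the control group and 52% in the SSDM group", two-sided alpha 0.05, power 90%, "20% attrition rate"; 1:1 allocation (SAP 6.1). Pooled-variance formula without continuity correction, mean rate 0.4815:

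n = [1.960 × √(2 × 0.4815 × 0.5185) + 1.282 × √(0.443 × 0.557 + 0.52 × 0.48)]² / 0.077² ≈ 883 per arm.

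Total 1766; 1766 / 0.80 = 2208, against 2200 stated, so the figure reproduces. It implies about 880 completers per arm (1100 × 0.80). No SD, correlation or power is given for any continuous endpoint, so the rest uses stated assumptions.

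**Precision lost by using change.** Let baseline SD be σ, follow-up SD also σ, and r their correlation. Per patient, the variance is 2σ²(1 − r) for change and σ²(1 − r²) after baseline adjustment. The ratio is (1 + r)/2.

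| Assumed r | Variance ratio | Equivalent extra patients, 2/(1 + r) − 1 | Interval narrower by, 1 − √ratio |
|---|---|---|---|
| 0.4 | 0.70 | 43% | 16% |
| 0.5 | 0.75 | 33% | 13% |
| 0.6 | 0.80 | 25% | 11% |
| 0.7 | 0.85 | 18% | 8% |
| 0.8 | 0.90 | 11% | 5% |

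The direction does not need equal variances. With follow-up SD kσ, the change variance minus the adjusted variance is σ²(1 + k² − 2rk) − k²σ²(1 − r²) = σ²(1 − rk)², which is never negative. The size does depend on k. The formula concerns means; the gain from adding baseline to a quantile regression would differ.

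**Does the pretest settle the branch?** In the joint-count simulation below, Kolmogorov-Smirnov rejected normality in every run. For normal values rounded to integers (880 observations) it rejected in 100% of runs at SD 2 or 4, 14% at SD 8 and 2% at SD 12. Discreteness alone therefore does not force the median branch for wide-range scores.

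**Joint counts.** Simulation with 880 completers per arm and 22 centres (SAP 6.1). Assumed: negative-binomial counts capped at 28, dispersion 0.5 or 1, a 45% mean fall in controls, and a follow-up mean 20% lower with SSDM. The true mean difference before the cap is baseline mean × 0.55 × 0.20. Results are shares of runs, for dispersion 0.5 / 1.

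| Baseline mean | True mean difference | Raw median difference = 0 | Centre-adjusted median coefficient = 0 | Wilcoxon p < 0.05 |
|---|---|---|---|---|
| 1.5 | −0.165 | 1.00 / 0.99 | 1.00 / 1.00 | 0.34 / 0.57 |
| 2.5 | −0.275 | 1.00 / 0.56 | 1.00 / 1.00 | 0.53 / 0.63 |
| 4 | −0.44 | 0.41 / 0.98 | 1.00 / 1.00 | 0.41 / 0.72 |
| 6 | −0.66 | 0.69 / 0.26 | 0.80 / 0.50 | 0.51 / 0.78 |
| 8 | −0.88 | 0.84 / 0.44 | 0.50 / 0.20 | 0.59 / 0.81 |

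The raw and Wilcoxon columns use 200 runs; the regression column uses 10 and is coarse. At a mean of 1.5, a raw median difference of 0 and a significant Wilcoxon test occur together in at least 1.00 + 0.34 − 1 = 34% of runs (dispersion 0.5) or 0.99 + 0.57 − 1 = 56% (dispersion 1). At means of 6 to 8 the coefficient was 0 in 20 to 80% of runs and otherwise about −1.

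Across the ten scenarios, power was 0.27 to 0.81 for a t test on change, 0.34 to 0.81 for Wilcoxon on change, and 0.76 to 1.00 for a mean model adjusted for baseline only (ordinary standard errors). These gains exceed the first table because the simulated follow-up counts, having lower means, also vary less than baseline.

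**The case against.** The case for leaving the plan alone is reasonable. These are secondary endpoints, randomisation protects the comparison, and no bias is alleged. Centre is adjusted for in the median branch. A median is a defensible summary of skewed, zero-heavy scores, and moving to a mean difference changes what is estimated. A median difference of 0 with a significant Wilcoxon test is not a contradiction, because the two address different quantities. All of this stands, and it limits the weight of the point. None of it explains why baseline value and stratum are left out, or why the method should depend on a pretest.

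A reader might also infer more than the documents support:
- *That joint counts will mostly show a difference of 0.* This is likely at assumed means of about 1.5 to 4 but inconsistent at 6 to 8, and the documents give no joint-count distribution.
- *That about 40% of this trial's patients start in remission or low activity.* The 40% (491/1,232) in Protocol 3.4 is from an earlier cohort of SSDM users. This trial excludes existing users and enrols at any activity level, so the figure is only indicative.
- *That normality will almost always be rejected.* This held for simulated joint counts but need not hold for wide-range scores.
- *That baseline adjustment halves the standard error.* That needs follow-up variance well below baseline variance: with k = 0.5 and r = 0.5 the variance ratio is 0.1875/0.75 = 0.25. The documents give neither quantity.
- *That baseline data are thrown away.* A change score does use them, only inefficiently.

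**Conclusion.** The point holds for the choice of method and the missing covariates, both of which follow from the text of SAP 6.7 read with SAP 6.4 and Protocol 3.3. For mean differences the avoidable loss is moderate: adjusted variance is 0.70 to 0.90 of change-score variance, assuming equal variances and r between 0.4 and 0.8. No comparable figure is available for the median branch.

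The uninformative median difference for joint counts is a risk conditional on low baseline counts. It was examined only for joint counts and should not be extended to SDAI, CDAI, HADS or SF-36.

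The primary analysis and sample size are untouched. The change is worth making, but the trial's main conclusion does not depend on it.

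**What to change.** In SAP 6.7, remove the normality pretest as the basis for choosing a method. For SDAI, CDAI, TJC, SJC, HADS and SF-36, at month 6 and at month 12, prespecify one linear model of the follow-up value on arm, baseline value, DAS28-CRP randomisation stratum and centre, with robust standard errors. Report the adjusted mean difference with its 95% CI. This estimate and its standard error can be pooled over the imputed data sets as SAP 6.9 intends. Keep Wilcoxon and quantile regression as sensitivity analyses, and bring Protocol 3.6 into line.

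If the sponsor prefers medians as the effect measure, the minimum change is to add the baseline value and stratum to the planned quantile regression.

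The cost is SAP wording and modest programming, with no new data. The downside is that the mean model changes the reported effect from a median to a mean difference, which should be stated openly. SAP 6.4 already reports per-protocol counts at months 6 and 12, so the change should be dated. If outcomes by arm have been seen, the new model should be presented alongside the planned analysis and labelled as added later.

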#### 6.8 Safety Analyses

This study does not involve safety issues, so safety evaluation is not required. The perceived adverse events will be collected. The adverse events were not assessed for both trial arms and were not able to be compared between the two groups.

Adverse events are defined as any general lack of well-being, symptoms of illness, or laboratory parameters outside the normal range.

Serious adverse events are defined as any life-threatening or fatal event.

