### 3.7 Safety Evaluation

This study does not involve safety issue, so safety evaluation is not required. This study will collect adverse events on the treatment of RA.

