### 3.9 Management of Clinical Study

If the protocol is revised, only the corresponding revised part and the revised informed consent can be implemented after being reviewed and approved by the ethics committee, and a copy of the approval by the ethics committee of Peking University People's Hospital is required to be provided to the clinical inspector. If the protocol is revised to reduce the obvious risk of the subjects, it can be implemented immediately, but it must be submitted to the relevant departments and the ethics committee for the record as soon as possible.

If severe safety issues arise during the trial, or major mistakes in the clinical trial protocol were found during the trial, the sponsor or the administrative department should request termination or the trial.

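### SAP 6.8 treats only fatal or life-threatening events as serious, and the waiver of safety evaluation conflicts with other sections of the plan

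*Combined protocol and SAP*

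**What the plan says.** The only definition of seriousness is in SAP 6.8: "Serious adverse events are defined as any life-threatening or fatal event". The same section defines the wider class very broadly: "Adverse events are defined as any general lack of well-being, symptoms of illness, or laboratory parameters outside the normal range". Protocol 3.7 has no definition of either.

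Both documents set safety evaluation aside. Protocol 3.7: "This study does not involve safety issue, so safety evaluation is not required". SAP 6.8: "This study does not involve safety issues, so safety evaluation is not required". Both then say that events will be gathered: "This study will collect adverse events on the treatment of RA" in the protocol and "The perceived adverse events will be collected" in the SAP. SAP 6.8 adds: "The adverse events were not assessed for both trial arms and were not able to be compared between the two groups".

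Elsewhere, protocol 3.9 opens its termination clause with "If severe safety issues arise during the trial" and says that the sponsor or the administrative department should then ask for the trial to end. Amendment 1 adds app alerts for raised liver enzymes and abnormal white-cell counts. The number and rate of adverse events is a secondary endpoint in protocol 3.3(5) (item 10), SAP section 3 (item 11) and SAP 6.7.

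**The concern.** With two classes only, everything short of a fatal or life-threatening event falls into one group. A hospital admission for infection and a marginal laboratory value are then indistinguishable in the planned reporting. If the report gives an SAE count, or says that there were none, the figure covers a narrower set of events than the word suggests unless the definition is printed beside it.

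The waiver is a separate difficulty. The plan says that there is no safety matter to evaluate, yet it provides for termination on safety grounds, builds laboratory alerts into the app and lists adverse events as an endpoint. Sites and the sponsor cannot tell from this text whether anyone is meant to look at the accumulating events.

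**Working it through.** No figure in the plan bears on this point, and the sample size calculation does not enter it. The check is a reading of the sections against each other.

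**Step 1. Apply the SAP 6.8 definitions to hypothetical events.**

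| Event | Adverse event? | Serious? |
|---|---|---|
| Fatal infection | Yes | Yes |
| Admission for infection, life not threatened | Yes (symptoms of illness) | No |
| Reaction leaving lasting disability, life not threatened | Yes | No |
| Liver enzyme slightly above normal | Yes (laboratory value) | No |

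The last three rows receive the same label. All are within the scope of collection; none is marked as serious.

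**Step 2. Set the waiver against the other sections.**

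| Section | Content | Consistent with no safety evaluation? |
|---|---|---|
| Protocol 3.9 | Termination to be requested for severe safety issues | No: someone has to judge whether such issues exist |
| Amendment 1 | Alert at ALT or AST above twice the upper normal limit, or white-cell count below 2,000 or above 10,000 per mL | No: this is laboratory safety surveillance |
| Protocol 3.3(5), SAP section 3, SAP 6.7 | Number and rate of adverse events as a secondary endpoint | No: an endpoint has to be evaluated |

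Protocol 3.9 does not define its trigger, and no section describes a scheduled review or a route by which a site's report reaches those who would act.

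**Step 3. Ask where the events come from.** Protocol 3.3(2) describes entry of 33 types of perceived adverse reaction for the SSDM arm. The alerts of Amendment 1 are a function of the app. Rheumatologist reports are the other named source. The follow-up table in protocol 3.3(4) has no adverse event row, and control patients are told to attend at months 6 and 12. Control patients are offered the app only after month 6 (SAP 6.1), so during the randomised comparison symptom entry and alerts exist in one arm only. This agrees with the SAP 6.8 statement that events were not assessed in both arms. It also means that the secondary endpoint cannot be read as a comparison.

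**Step 4. Size.** The number of events labelled non-serious because of the narrow definition is the number of patients observed times the proportion with an event that is serious in the wider sense but neither fatal nor life-threatening. The planned enrolment is 2204. The proportion is not given, and the number effectively observed for adverse events is also unclear because ascertainment was not equal. The product cannot be computed from the documents, and any assumed rate would only return the assumption.

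**The case against.** The strongest reply is that this is a pragmatic trial of a self-assessment app, that events are collected, and that no SAE endpoint or SAE analysis is listed. The definition therefore feeds no planned result. That last part stands: the distortion arises only if an SAE count is reported. But the SAP does define the term, presumably for use, and the low-risk premise is not secure. Protocol 3.1 cites more frequent changes of DMARD therapy after nurse-led self-assessment, and protocol 3.3(5) lists active intervention by doctors as an endpoint, so the app may alter drug exposure.

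Three stronger readings are tempting and are not supported.

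- A reader might infer that serious harm goes uncounted. It does not: such events meet the broad adverse event definition and both documents provide for collection. They are not separated out.
- A reader might infer that the trial has a stopping rule that must be obeyed. Protocol 3.9 is a general clause that also covers major mistakes in the protocol. It says that termination should be requested, and it sets no threshold.
- A reader might infer that protocol 3.9 has nothing to act on, or that a run of admissions could not invoke it. Its wording is not tied to the SAE definition, and rheumatologist reports, symptom entries, alerts and the physicians' real-time view of app data all exist. What is absent is a defined trigger and a planned review.

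Nor does the mention of disability in protocol 3.1 help the argument: it describes RA without treatment, not harm from the intervention.

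**Conclusion.** The point holds as a defect of classification and of internal consistency. Under SAP 6.8, events that cause admission or lasting disability without threatening life are not identified as serious, and any SAE count would exclude them by definition. The statements that safety evaluation is unnecessary contradict protocol 3.9, Amendment 1 and the adverse event endpoint, and these passages must be reconciled.

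The number of events affected is unknown. The conclusion rests on the written definitions alone and on no wider category standing elsewhere in the plan; none was found. The primary endpoint and its analysis are not affected. The change should be made because the safety statements cannot be interpreted as they stand.

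**What to change.** 1. In SAP 6.8 and protocol 3.7, extend the definition of serious to events that cause or prolong hospitalisation, cause persistent disability or are otherwise medically important, alongside fatal and life-threatening events. SAP 6.4 already gives realised per-protocol counts at months 6 and 12, so new site reporting may come too late for much of this trial. Apply the wider definition to adverse events already collected where the records allow.
2. Replace the waiver in both sections with text consistent with protocol 3.9: sites report SAEs to the sponsor, and the existing study team reviews the cumulative listing. Any criterion for termination is for the sponsor to settle when it reconciles the passages.
3. Beside any SAE or adverse event count, print the definition used. State that events were not assessed in both arms and that alerts and symptom entry exist only for app users, so the counts must not be read as a between-arm comparison. Align the secondary endpoint entries in protocol 3.3(5), SAP section 3 and SAP 6.7 with that statement.

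The cost is wording in a few sections and a short SAE form, with no added visits, tests or committee. The downside is more SAE reports to process, and some collected records may lack the detail needed for reclassification.
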